### Statistical analysis plan

For the data analysis, cross-sectional and longitudinal analytical methods will be employed using established statistical software. Longitudinal regression models (e.g., Mixed-Model with Repeated Measures (MMRM) will be used, allowing flexible modeling of endpoints while incorporating potential confounders should differences between the intervention group (IG) and control group (CG) exist in relevant influencing variables despite randomization. Through a multi-level approach, the clustering of individuals within the transplant centers (differences in intervention effect by center) can be accounted for, and the analyses can be additionally adjusted for confounders at the transplant center level (e.g., number of transplants per year, experience with telemedicine). Longitudinal analyses will be applied for the endpoints of improved quality of life and improved disease management. Depending on the scale level of the dependent variables, linear or logistic regressions will be calculated. For the incremental cost-effectiveness analysis, the ratio of the cost difference (estimated additional costs of the new care model compared to standard care) to the benefit difference between IG (with new care) and CG (without new care) will be calculated (ICER).

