**Figure 1 f1:**
[figure not shown]
Study design.

All patients will receive the same routine post-transplant aftercare. Patients in the interventional arm will receive predefined additional telemedical management, including regular telemedicine visits and automatic data transfer (vital signs, wellbeing, medication plan, laboratory data, and chat) between the patient at home and a KTC through a certified smartphone application. Furthermore, the home nephrologists of patients in the interventional arm will be invited to participate in the automatic data transfer of key variables (such as vital signs and laboratory data) with the KTC. A separate telemedicine team will constantly review the incoming data according to a predefined protocol and eventually contact the patient and/or the home nephrologist to start appropriate interventions. For patients in the interventional arm, physicians will use the certified iBox score based on the “iBox” algorithm (Predict4Health, Paris, France) to better detect patients at risk for early graft failure. In the interventional arm, drug-drug interactions will be regularly checked with the help of certified software (ID Medics^®^, GmbH & Co. KGaA, Berlin, Germany).

It has been previously demonstrated that additional telemedical care may affect a variety of important key outcome variables for long-term success after kidney transplantation (22, 52, 53). In our trial, we chose a composite endpoint of such variables as the primary outcome. Under the assumption of a small to medium effect size of Cohen’s d = 0,31, we calculated that 192 patients per group (including a 20% drop-out rate) are needed to show a difference between groups. Thus, the study population will consist of approximately 384 KTRs, irrespective of age. They will undergo central web-based randomized placement in one of the two treatment groups in a 1:1 ratio. Because expected key outcomes (e.g., hospitalization rate and adherence) may differ according to the age of participants and the time post-transplant, we will stratify them at randomization not only by KTC, but also according to patients’ age: 18–65 years and >65 years. Randomization of children was stratified only by age and not by KTC because of the low expected number of children per KTC (< 12 years, 12 to 18 years).

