### Randomization

Randomization will be performed using a predefined variable block randomization scheme, stratified by the participating centers and the age of the participant. Due to low expected patient numbers in the age groups of < 12 years and 12 to 18 years, patients in these age groups will be randomly stratified by age, but not by KTC. The randomization scheme will be generated and reviewed by the study biostatistician and quality assurance staff and locked by them after approval. The investigation sites will assign eligible patients through an interactive internet-based computer system (IWRS) once a patient has satisfied the requirements to be included in the study. The IWRS randomization tool is part of the eCRF (Secutrial^®^, interActive Systems, Berlin, Germany). After screening for eligibility and assignment of the individual PID, each patient can only be assigned once to one of the treatment arms. Using the web-based tool will make it impossible for the study personnel to predict the assignment. The sites will record the time of randomization. Treatment in the assigned group starts in the first year after the kidney transplantation and ends in month 12 after randomization.

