### Study endpoints

The primary endpoint will be measured via seven indicators: BAASIS Score (adherent) after 12 months, IPV of tacrolimus trough levels < 30% between months 6 and 12, number of unplanned hospitalizations in 12 months, number of unplanned hospitalizations > 10 nights in 12 months, normal 24h blood pressure profile at 12 months, no *de novo* DSA at 12 months, and eGFR ≥ 45ml/min at 12 months. Each indicator of the primary endpoint can be defined as achieved (=1) or not achieved (=0) for each patient. The primary endpoint is calculated by an unweighted sum of the achievement of the indicators (min = 0, max = 7). Secondary endpoints were graft failure within 12 months, better iBox prognosis at 12 months, increase in quality of life (self-report) over 12 months, increase in illness management (self-report) over 12 months, and incremental cost-effectiveness. In addition, acceptance of the patients and the telemedicine teams of the new telemedical approach will be measured.

*Adherence* will be determined by the BAASIS questionnaire (38) at month 12. Non-adherence is defined as “yes” to any of the questions. For patients without valid responses to the questionnaire, the response to the BAASIS questionnaire at month 9 will be imputed. Patients who did not respond to the questionnaire at months 9 and 12 will be considered non-adherent.

*Tacrolimus IPV* will be determined from tacrolimus trough levels at months 6, 7.5, 9, 10.5, and 12. To determine tacrolimus trough levels at months 7.5 and 10.5, patients will undergo a blood draw at home (either nephrologist or a general practitioner) or at a KTC according to the patient’s decision. If necessary, whole blood will be shipped by mail to the transplant center for central evaluation. For patients with tacrolimus levels of less than 3 (except for patients with graft loss or switch to another immunosuppressant), high tacrolimus IPV will be assumed.

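### Patient-level adjustment is tied to observed differences between the arms instead of to covariates fixed in advance

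*Protocol article*

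**What the plan says.** The Statistical analysis plan section of the protocol article introduces longitudinal regression models, with MMRM as the example, as a flexible way of modelling endpoints while "incorporating potential confounders should differences between the intervention group (IG) and control group (CG) exist in relevant influencing variables despite randomization". It does not say how large a difference must be, how it is judged, or which variables count as relevant.

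Three other statements in that section and under Study endpoints set the reach of this clause:

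- The longitudinal models are assigned as follows: "Longitudinal analyses will be applied for the endpoints of improved quality of life and improved disease management". Both are secondary endpoints.
- Centre is handled separately. Through a multi-level approach, "the clustering of individuals within the transplant centers (differences in intervention effect by center) can be accounted for". This is optional and not linked to imbalance.
- The primary outcome is a single score per patient: "The primary endpoint is calculated by an unweighted sum of the achievement of the indicators (min = 0, max = 7"). No model is named for it, and no other rule for patient-level covariates is given.

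On design, the Randomization section describes a variable block scheme "stratified by the participating centers and the age of the participant", with children stratified by age only. The stratification paragraph in Methods and analysis gives the reason: "expected key outcomes (e.g., hospitalization rate and adherence) may differ according to the age of participants and the time post-transplant". Time post-transplant appears in that reason but is not a stratum.

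**The concern.** In a properly randomized trial, a baseline difference between the arms is chance. What makes a covariate worth including is how strongly it predicts the outcome, not whether it happens to differ. A rule triggered by imbalance has three weaknesses here.

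- **Timing.** The model is settled after arm-level baseline data have been seen, and the missing threshold and list leave the decision to judgement.
- **Precision.** A strong predictor that happens to be balanced is left out, so most of the available gain is lost.
- **Fit with the design.** Age group is balanced by the stratified blocks, so the trigger would rarely bring it in. Time post-transplant is treated as prognostic in the design, and patients may enter at any point within 12 months of transplantation. Yet it is neither balanced by design nor certain to be adjusted for.

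**Working it through.** **Inputs from the article (Methods and analysis).** "small to medium effect size of Cohen’s d = 0,31"; 192 patients per group including 20% drop-out; 1:1 allocation.

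**Assumed, because the article does not state them.** Two-sided 5% test; share of outcome variance explained by covariates (R²) from 0 to 0.30.

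**1. The stated sample size.** n per arm = 2(z₁₋α/₂ + z_power)²/d². At two-sided 5% and 80% power this is 2(1.960 + 0.842)²/0.31² = 164 after rounding up. Dividing by 0.8 gives 205; multiplying by 1.2 gives 197. One-sided 5% with 85% power gives 150, then 150/0.8 = 188. None of these is exactly 192, and the article states no alpha, sidedness or power, so the figure cannot be reproduced with certainty. This point does not depend on it. Evaluable patients: 192 × 0.8 = 153.6, about 154 per arm.

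**2. Power when covariates are always included.** Power = Φ(d·√(n/2)/√(1 − R²) − 1.960), with d·√(n/2) = 0.31 × √77 = 2.720.

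| R² (assumed) | 2.720/√(1 − R²) | Power |
|---|---|---|
| 0 (unadjusted) | 2.720 | 77.6% |
| 0.05 | 2.791 | 79.7% |
| 0.10 | 2.867 | 81.8% |
| 0.20 | 3.041 | 86.0% |
| 0.30 | 3.251 | 90.2% |

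**3. How often the trigger fires.** The article gives no threshold, so p < 0.05 for imbalance is assumed. A given covariate then enters in about 5% of trials. At least one of five independent covariates enters in 1 − 0.95⁵ = 23%, and at least one of ten in 1 − 0.95¹⁰ = 40%.

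**4. Simulation of the three rules.** 20,000 trials per setting, 154 per arm, simple 1:1 randomization, normal outcome, one or five normal covariates jointly explaining R². The Monte Carlo standard error is about √(0.78 × 0.22/20,000) = 0.3 points for power and √(0.05 × 0.95/20,000) = 0.15 points for type I error.

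| R², covariates | Power: never | Power: triggered | Power: always | Type I: never | Type I: triggered | Type I: always |
|---|---|---|---|---|---|---|
| 0.10, one | 76.7% | 77.2% | 80.9% | 5.1% | 4.8% | 5.1% |
| 0.10, five | 77.8% | 78.0% | 81.4% | 5.0% | 4.8% | 5.0% |
| 0.30, one | 77.6% | 79.0% | 89.9% | 5.0% | 4.2% | 5.0% |
| 0.30, five | 77.2% | 78.3% | 89.4% | 4.9% | 4.2% | 5.1% |

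At R² = 0.30 with one covariate, the trigger recovers (79.0 − 77.6)/(89.9 − 77.6) = 1.4/12.3, about 11% of the available gain. The other settings are of the same order or lower.

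**5. Discretion over reporting.** If the more favourable of the unadjusted and fully adjusted p-values could be reported, type I error would be 6.6% at R² = 0.10 and 7.5% at R² = 0.30. This is a different procedure from a fixed trigger.

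**The case against.** The strongest reply is that this is a condensed article without its full analysis plan, so a missing covariate list is not a fault. That stands, and the point does not rest on it. The data-dependent condition is itself stated, and an analysis plan that followed it would inherit the weakness. It is also fair that the sentence says what the models allow. It does not say that no covariate can enter otherwise.

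Several stronger readings are tempting but not supported:

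- **That the rule governs the primary analysis.** The clause belongs to longitudinal models, and these are assigned to two secondary endpoints. Extending it to the primary score is an inference from the general word for endpoints and from the absence of any other rule.
- **That the strata are ignored.** Centre has its own optional route. Age group is the stratum that the analysis text does not mention. No size can be put on any resulting error in the standard error.
- **That type I error is inflated.** A fixed trigger is slightly conservative. Inflation would need freedom to choose which result to report. The missing threshold leaves room for that, but the article does not plan it.
- **That a large power gain is assured.** R² is assumed. The two hospitalization indicators, de novo DSA and tacrolimus variability all arise during follow-up, so four of the seven components have no direct baseline counterpart. The gain may lie at the low end.
- **That every useful covariate is already collected.** The article does not confirm BAASIS or 24-hour blood pressure at baseline, and the visit plan it refers to is not shown.

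**Conclusion.** The point holds in limited form. The article states an imbalance-driven rule for patient-level adjustment, without a threshold or list, and that is a poor basis for choosing covariates. Its stated setting is the longitudinal models for quality of life and disease management. For the primary score, the gap is that no other patient-level rule is given.

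The cost is mainly precision. Against 77.6% unadjusted, always adjusting adds about 2 points of power at R² = 0.05 (79.7 − 77.6) and about 13 at R² = 0.30 (90.2 − 77.6) by formula, or about 12 in simulation. The trigger adds at most about 1.4 points in the settings tried.

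These figures assume a two-sided 5% test, normal outcomes, simple randomization and a p < 0.05 trigger. They use the effect size planned for the primary score, so for the secondary endpoints they are illustrative only. The remaining cost is avoidable discretion after arm-level data are seen. This should be fixed, but it does not by itself threaten the validity of the trial.

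**What to change.** Before arm-level data are examined, replace the conditional clause with a covariate set fixed in advance, included whatever imbalance is observed, for the primary score and the secondary endpoints:

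- the randomization strata (centre by age group for adults, the two age groups for children);
- time since transplantation at randomization;
- baseline eGFR;
- the baseline value of the outcome, or of a component of the score, where it is collected. Quality of life and illness management are defined as increases over 12 months, which implies a baseline value. BAASIS and blood pressure should be listed only if the visit plan confirms a baseline measurement, and blood pressure in a form comparable between adults and children.

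Keep imbalance-driven adjustment as a sensitivity analysis only.

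The cost is analysis-plan wording, with no new patients or visits. Centre and age group are needed for randomization, and eGFR and time since transplantation for eligibility. Trial status expects the last patient out on 30 April 2026. The article cannot show whether arm-level data have since been examined. If they have, the date on which the covariate set was fixed should be reported.

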## Discussion

This study will provide novel fundamental data on whether additional interventional telemedical management will lead to a higher chance for long-term graft survival, increase adherence and QoL, and reduce complications and healthcare costs after kidney transplantation. As intended by the German Government, this study has the potential to optimize post-transplant care in Germany. If successful, our program will be extended to other transplanted organs and to all regions of Germany and the costs of positively evaluated elements will be covered by public health insurance companies. If our study is successfully completed, it could provide valuable information for the post-transplant management of KTR. Several pitfalls were taken into consideration. Since younger people are more digitally native, we had a concern that older KTRs would be disadvantaged, however, we approached all age groups and did not find that older patients had problems. Since this study represents a holistic approach, a primary endpoint based on seven indicators was chosen as the intervention does not primarily focus on one of them, but may result in unique effects on these indicators for each patient. By not focusing on a single variable, we account for these potentially differential effects of smartNTx. In combination, achieving as many of these indicators as possible represents a valid measurement of stable kidney function, adequate illness behavior, and a good health situation for the patients.

## Trial status

The trial has been registered at ClinicalTrials.gov: NCT05897047. The results of the trial will be published independent from outcome and results. Negative results will be published as well. Recruitment started in May 2023 and finished in April 2025. The last patient in was on 30 April 2025 and the last patient out is expected on 30 April 2026. At the timepoint of initial submission (15.02.2024) 327 patients had been randomized. At the timepoint of submission of revision, 391 patients were randomized so the required number of recruited patients was reached.
